### Recruitment {15}

Participants will be recruited by established strategies via advertisement in local media (e.g., newspaper, brochures) and using an already existing data pool of older adults from other studies. This recruitment strategy has been successful in the past in other projects. In addition, flyers are displayed in public local places (shops, library and physicians) as well as advertisements in public transportation.

## Assignment of interventions: allocation

### Sequence generation {16a}

Randomization will be stratified by gender, and statin intake, to ensure equal distribution between both groups, while couples will be block-wise randomized to ensure participation together in one group. The randomization lists with block sizes 4, 6, and 8 were computer-generated via an online tool (Sealed Envelope Ltd. 2021. Create a blocked randomization list ([Online] Available from: https://www.sealedenvelope.com/simple-randomiser/v1/lists [Accessed 12 Aug 2022] [63] by study personnel who was otherwise not involved in the planning of the study design).

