### Sham control group

The sham control intervention will occur in the same frequency as the multi-component exercise intervention, over a 16-week period (as mentioned previously). Each session will contain a 40-min educational presentation and 20 min of light upper extremity stretching. In the SCG, the groups sizes will vary between 20 and 30 participants. As a fundamental aspect, the SCG will receive light stretching exercise and strength training of the upper extremities. Second part of the control intervention will be educational health lectures, as previously described before [61]. Topics of the educational and light stretching training sessions are detailed in Table 3.

**Table 3 Tab3:** Topics of the control intervention

*Domain*	*Topic*

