### Strategies to improve adherence to interventions {11c}

For saliva sampling, which will be undertaken by the participants themselves, personal meeting includes explanation and practical instruction of saliva sampling procedure. A detailed set of written instructions and a brief questionnaire asking participants for sampling times for reference at home are provided at this first appointment at IBA. If saliva samples were not returned after certain time, close communication via phone calls will be applied. Participants receive personal reminder calls for the assessments and testing appointments, if desired.

The participants will be introduced to each other during the intervention sessions to enable social bonding to the program. Special efforts will be made to keep the participants of the SCG in the project by handing out birthday cards and celebrating Christmas at a special event together.

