### Sample size {14}

Calculation of optimal sample size is based on two sets of available information. First, the required sample size for successful reduction of CaF was computed, and second, the required sample size for reduction of inflammatory markers in consequence of successful interventions was computed.

The authors are rather confident with regard to reduction of CaF: Based on previous intervention studies using similar procedures [54–56], a small-to-medium effect of around *f* = 0.15 is expected for reduction of CaF (indicated by FES-I). A priori power analyses using G-POWER (3.1.9.2.) assuming a statistical power of 0.95 and alpha error probability of 0.05 (assumed correlation among repeated measures of 0.50, and non-sphericity criterion ϵ set to 1). This indicates that *n* = 154 participants will need to be enrolled to achieve a successful reduction of CaF. Based on a drop-out rate of about 25–30% [56], *n* = 200 participants need to be randomly assigned to a group (i.e., *n* = 100 per group).

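### The 0.95 power in {14} assumes independent participants, but couples are randomised as a unit and treatment is delivered in groups

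*Protocol article*

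**What the plan says.** **Allocation.** Under Sequence generation {16a}, "couples will be block-wise randomized to ensure participation together in one group". Study procedure, under {11a}, makes participation together as a couple one level of the gender stratification factor. For couples, then, the unit allocated is the pair. The expected share of couples is not given.

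**Delivery.** Under Sham control group: "In the SCG, the groups sizes will vary between 20 and 30 participants". With 100 per arm this means about 3 to 5 control groups (100/30 = 3.3; 100/20 = 5). The intervention group (IG) is also taught in supervised sessions, but its class size is not stated. Under {11c}: "The participants will be introduced to each other during the intervention sessions to enable social bonding to the program".

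**Sample size {14}.** For the Falls Efficacy Scale–International (FES-I), "a small-to-medium effect of around *f* = 0.15 is expected for reduction of CaF (indicated by FES-I"). The other inputs are a power of 0.95, an alpha of 0.05, and "assumed correlation among repeated measures of 0.50, and non-sphericity criterion ϵ set to 1". The result is 154 participants, raised to 200 for a drop-out of 25–30%. No input describes correlation between participants.

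**Analysis.** {20a} says that the reduction in FES-I at T1 will be compared with control. It names no model and points to a preregistration that is not shown. {20c} limits the analysis to adherent participants.

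**The concern.** Two partners allocated together do not supply two independent pieces of information on the treatment effect. People taught in the same class can share influences on FES-I, stress and attendance, and that shared variance does not shrink as more people join a class. Both kinds of dependence act on the between-arm comparison. The correlation of 0.50 in {14} is a different quantity: it links repeated measures on one person.

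Two things are at stake. The claimed 0.95 power would be too high. And if the eventual model also left out couple and group, its standard errors would be too small and its type I error above 5%. {14} leaves little room to absorb this, because the numbers expected after drop-out already fall below the stated requirement.

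**Working it through.** **Inputs from the protocol:** f = 0.15, alpha 0.05, power 0.95, within-person correlation 0.50, ϵ = 1, 154 required, 200 randomised 1:1, drop-out 25–30%, sham control group (SCG) classes of 20–30.

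**Assumptions, not in the protocol:** two time points (T0, T1; the number used is not stated, but the primary outcome is at T1); 10–40% of participants in couples with partner ICC 0.2–0.4; training-group ICC 0.01–0.05; SCG classes of about 25; IG classes of about 10; 75% of each class analysed.

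**1. The plan's own figure.** For the group-by-time interaction in a repeated-measures ANOVA, the noncentrality is λ = f² × N × m / (1 − ρ), with m time points. For m = 2, λ = 0.0225 × N × 2 / 0.5 = 0.09N. Power of 0.95 needs N = 147 (148 with equal arms); m = 3 needs 116. Neither equals 154, although f = 0.147 with m = 2 or f = 0.13 with m = 3 returns it, and f is given only as an approximate value. At N = 154 and m = 2 the power is 0.959, close to that claimed. None of the variants tried contains a clustering allowance.

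**2. Slack.** 200 × 0.75 = 150 and 200 × 0.70 = 140, both below 154. With m = 2 the power is 0.955 and 0.941 before any clustering.

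**3. Effect scale.** λ = 0.09N corresponds to a standardised difference d in change with d²N/4 = 0.09N, so d = 0.6.

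**4. Couples alone.** For pairs in the same arm, design effect (DE) ≈ 1 + share × ICC.
- Low: 1 + 0.10 × 0.2 = 1.02. High: 1 + 0.40 × 0.4 = 1.16.
- A standard error that ignored couples would need multiplying by √DE = 1.01 to 1.08.
- Dividing λ by DE at N = 150 gives power of 0.951 to 0.924.

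**5. Training groups.** DE = 1 + (k − 1) × ICC in each arm, with k the number analysed per class: 25 × 0.75 = 18.75 (SCG) and 10 × 0.75 = 7.5 (IG), averaged over arms. Naive type I error = 2[1 − Φ(1.96/√DE)]. Power = Φ(0.6 × √(150/4)/√DE − 1.96).

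| Group ICC | DE, SCG | DE, IG | Average DE | Naive type I error | Power |
|---|---|---|---|---|---|
| 0.01 | 1.18 | 1.07 | 1.12 | 6% | 0.93 |
| 0.02 | 1.36 | 1.13 | 1.24 | 8% | 0.91 |
| 0.05 | 1.89 | 1.33 | 1.61 | 12% | 0.83 |

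If IG classes were also about 25, an ICC of 0.05 would give DE 1.89, naive type I error of 15% and power of 0.76.

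**6. Sensitivity to the number of time points.** With m = 3 and 150 analysed, power is 0.985 without clustering, about 0.96 at DE 1.24, and about 0.90 at DE 1.61.

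**7. Few control groups.** The power in step 5 uses a normal critical value. A simulated Welch test on class means (8 IG and 4 SCG classes, 75 analysed per arm, d = 0.6) gave power of about 0.88 at ICC 0, and 0.84, 0.79 and 0.68 at ICC 0.01, 0.02 and 0.05. It approximates a primary model with a group term and small-sample degrees of freedom.

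**The case against.** A reader might infer that the analysis will treat 200 people as independent, so that the confidence intervals will be too narrow. The documents do not support that. {20a} names no primary model, and a condensed article may leave the model to an analysis plan or preregistration. {14} does name bivariate correlation and multiple linear regression, but for the association hypotheses, not for the primary comparison. The calculation rests on 154, 200 being the number randomised, and the analysis is per protocol. The statement about standard errors is therefore conditional.

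The group ICC may also be low. Classes are formed after randomisation, all delivery is at one institute, balance exercises and ankle weights are tailored to the individual, and from week 5 home sessions outnumber supervised ones. The bonding described in {11c} is to the programme, and no passage ties an instructor to a class. Every clustering value used here is assumed, and couples alone have a small effect. The article is dated March 2024 with recruitment ending in May 2024, so restating the power cannot change N. With about 3 to 5 SCG classes, a group variance estimated separately by arm would be very imprecise.

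All of this stands, and it limits the size of the point and the form of the remedy. It does not answer the omission in {14}. That power statement is given in full, and it assumes independence although the same article allocates pairs and teaches in groups.

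**Conclusion.** The point holds for the sample size, and conditionally for the analysis. The stated 0.95 power carries no allowance for couples or training groups, and 140 to 150 analysed participants leave no slack in a two-time-point calculation.

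The likely loss from couples alone is slight: power of about 0.95 to 0.92. Training groups could matter more: power of about 0.93 to 0.83, and naive type I error of about 6 to 12%, for ICCs of 0.01 to 0.05 with SCG classes of about 25 and IG classes of about 10. These powers precede any small-sample degrees-of-freedom correction, which would lower them further. Three time points would make the loss smaller. No single figure can be given, because the ICCs, the couple share and the IG class size are not in the documents. Whether the reported intervals would be too narrow depends on positive ICCs and on a primary model that ignores them.

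**What to change.** - Record a couple identifier and a training-group identifier for every participant. Couples are known at randomisation and attendance is monitored at each session, so this costs little.
- In the primary FES-I analysis, account for couple as the randomised unit, by a random intercept or cluster-robust standard errors.
- Account for training group with one simple random intercept and small-sample degrees of freedom. Do this at least as a sensitivity analysis, since about 3 to 5 SCG groups support little more.
- In {14}, state the number of time points used and restate the power with a design effect over a stated range of ICC, couple share and group size in both arms. Leave N unchanged.

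The price is wider intervals and a less favourable stated power. If the group term goes into the primary model, the loss of degrees of freedom is marked: in the class-level simulation, power was about 0.88 even with no group effect at all. That is the reason to allow the group term to sit in a sensitivity analysis.

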### Concealment mechanism {16b}

The randomizing person receives only the stratification information to assign the intervention. The allocation sequence is hidden in a read-only, password-protected spreadsheet. The revelation of a new group allocation is automatically documented by the system including username, date, and time. Exposed group allocations cannot be altered or erased. The recruiting team has no access to the randomization list.

### Implementation {16c}

After signing the written, informed consent and completing baseline assessments during the first in-person visit conducted by trained study staff, randomization is carried out by enrolling participants in concealed randomization lists by a separate member of the intervention team who only receives the necessary information for stratification.

## Assignment of interventions: blinding

### Who will be blinded {17a}

The study will be conducted as a double-blind study. Participants will be randomized into either the IG or the SCG with the information that the aim of the study is to compare two different intervention methods. While each employee of the project can perform recruitment and baseline assessment, the personnel at the IBA will solely conduct the intervention. The Department of Health Psychology will be responsible for the outcome assessment, allowing for blinding with regard to group allocation of the participants. All biological specimens are labeled by a participant code only, which allows blinding during laboratory analysis.

### Procedure for unblinding if needed {17b}

We do not anticipate any requirement for unblinding, but, if required, the principal investigator will have access to group allocations, and any unblinding will be reported.

## Data collection and management

### Plans for assessment and collection of outcomes {18a}

Data collection procedure is shown in Table 4. Except of sociodemographic characteristics and cognitive function, all questionnaires and laboratory and functional tests are performed in-person at each visit, respectively. Data collection will be finished in the 2nd quarter of 2025.

After completing data collection for each time point, data entry will be performed contemporaneously to ensure identification of missing data and any discrepancies. This enables to record missing data or incorrect inputs from participants. Prior to hypothesis testing, all data will be cleaned, inspected for outliers, and tested for normality of distribution. Composite scores will be computed were appropriate, e.g., for questionnaires. Laboratory data will be quality checked using standard procedures, including intra- and inter-assay variability. All biomarkers will be analyzed in duplicates, as is done in standard procedures in the laboratory. Laboratory values not complying with quality control requirements will be repeated. Means and standard deviations for all variables will be computed, and preliminary analyses testing for age and gender effects, pre-intervention group differences, and time effects of repeated samples will be performed.

### Plans to promote participant retention and complete follow-up {18b}

Each participant receives their own data at each in-person visit as well as a summary of all their data at the end of the study. Reminder calls and appointment invitations are sent to promote participant completion of the intervention and follow-up assessments.

### Data management {19}

With regard to data management, we will follow the current research data policy of Friedrich-Alexander-Universität Erlangen-Nürnberg (released in December 2019). All data will be handled in compliance with current German and European data protection laws and will be subject to our standardized data safety and monitoring plan. Ethics approval has been obtained from the local IRB (“Ethikkommission der Medizinischen Fakultät der FAU”), #317_20B, August 26, 2020, and all data collection, storage, and the local data protection authority (“Datenschutzbeauftragter der FAU”) will evaluate protection procedures. The study protocol complies with the Declaration of Helsinki and Guidelines for Good Clinical Practice. This study follows the FAIR principles (“Findable, Accessible, Interoperable und Re-Usable”) for data management. All data will be pseudonymized, i.e., a numerical code will be generated and used as a data identifier. Personal information will be stored in data file separate from all other data, and only the principal investigators will have access to identifying personal information. Participants will be granted the right to ask for their data to be deleted as long as the data is not completely anonymized. One year after completion of data analyses, all personal information will be destroyed. De-identified data will be stored on secure file servers for 10 years according to DFG recommendations. De-identified data will be made available through a public repository to be defined (e.g., ZPID). Data monitoring protocols will be established to ensure that any adverse events are reported by study coordinators and PhD students to the responsible PI (Drs. [name] and [name] for the intervention part, [name]. [name] for the laboratory part). Responsible PIs will notify the relevant supervising bodies (IRB; data protection authority) within 1 week. All PIs will establish a monthly data safety meeting. Data entry will be double-checked by a trained study nurse and staff of the IBA to guarantee correctness, completeness and plausibility of the provided information. The record of the results in the electronic database and its countercheck should be performed within 1 month of the elicitation to enable a re-collection of missing or wrong inputs from the participants. After completion, the anonymized electronic database will be made available for other researchers upon request. It will be checked if the database could also be saved in a public repository (e.g., DRYAD https://datadryad.org/).

### Confidentiality {27}

Separately from all other data, personal information will be stored in a password-protected data file.

### Plans for collection, laboratory evaluation and storage of biological specimens for genetic or molecular analysis in this trial/future use {33}

Saliva and blood samples will be collected and stored at specific temperatures for analysis. Saliva samples will be taken at IBA and kept at – 20 °C, while blood samples will be stored at − 80 °C after subsequent processing. Laboratory analysis will take place at shared facilities between the IBA and the Chair of Health Psychology following the completion of sample collection. All biological samples will be preserved for potential re-analysis until the end of the study.

## Statistical methods

### Statistical methods for primary and secondary outcomes {20a}

IBM SPSS® Statistics for Windows, Version 29 software (IBM Corp., Armonk, NY, U.S.) will be used for all statistical analyses. Descriptive statistical analysis will be performed for participants’ characteristics as mean ± standard deviation or median and interquartile difference for continuous variables. Absolute numbers and percentages will be presented for dichotomous and categorical variables. Prior to data analyses, data will be checked for outliers and normality. For the evaluation of primary outcome, the reduction of CaF at T1 will be investigated by FES-I Score in comparison to CG.

All hypotheses of this study are described in detail in the “Objectives {7}” section and are preregistered at https://osf.io/m84hq.

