### Intervention description {11a}

#### Study procedure

The general study design is that of a randomized controlled trial. After screening and providing written, informed consent, eligible participants will be randomized to participate in either the IG or the SCG of a 16-week intervention period (described in detail below). Randomization will be stratified by gender (female, male, or together as a couple), and statin intake, to ensure equal distribution between both groups. For each group, the intervention or control treatment will be followed by an 8-month follow-up period. This design allows to include 3 data collection time points: T0 at baseline, T1 after intervention or control treatment, T2 at 8 months post intervention. Post-intervention follow-up intervals are selected based on the anticipated trajectories of the development of psychological and psychobiological changes.

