### Outcomes {12}

As the primary outcome, the decrease in CaF after intervention (T1) measured by FES-I score in comparison to the SCG will be confirmed. All secondary outcome measures will be assessed at three time points (T0, T1, and T2) and changes between groups over time will be explored. Therefore, sarcopenia will be assessed by BIA, physical function will be tested by SPPB, and handgrip strength and physical activity will be tested by actigraphy. The VAS scale of EQ-5D will determine health-related quality of life. General psychological status will be explored with questionnaires for depression (GDS), perceived stress (PSS), and anxiety (GAS). Furthermore, MMSE and TMT A and B will determine cognitive function.

Pathophysiological parameters changes will be explored in blood samples such as levels of CRP, IL-6, TNF-alpha, and IL-10 for systemic inflammatory processes as well as gene expression of IL-1beta, IL-6, IL-10, and I-kappa B for intracellular inflammatory activity. In addition, stress system activity will be measured by changes in cortisol and alpha-amylase levels in salivary samples.

If a fall or accident resulting in severe injuries (e.g., fractures) occurs during the intervention period, it poses a potential risk to the participants and is therefore considered an adverse outcome.

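### The primary FES-I comparison names no model, and its sizing points to an unadjusted change score; prespecified adjustment for baseline FES-I would be worth about a third more participants at the protocol's assumed correlation

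*Protocol article*

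**What the plan says.** Section {12} of the protocol article defines the primary outcome: "the decrease in CaF after intervention (T1) measured by FES-I score in comparison to the SCG will be confirmed". The methods section, {20a}, repeats this as "the reduction of CaF at T1 will be investigated by FES-I Score in comparison to CG". It names no model, covariate or effect measure, and for the hypotheses it points to the objectives and the preregistration.

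Three other sections bear on the analysis:

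- **Sample size {14}.** A G*Power calculation with f = 0.15, "assuming a statistical power of 0.95 and alpha error probability of 0.05" and "assumed correlation among repeated measures of 0.50" leads to 154 participants. The number of time points is not given.
- **Plans for assessment and collection of outcomes {18a}.** Among the steps around data cleaning, "preliminary analyses testing for age and gender effects, pre-intervention group differences, and time effects of repeated samples will be performed".
- **Study procedure and Sequence generation {16a}.** "Randomization will be stratified by gender (female, male, or together as a couple), and statin intake"; couples are allocated together. No section carries these factors into an analysis.

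**The concern.** The text describes a reduction compared between arms, and the sizing uses a repeated-measures test. Together they read most naturally as an unadjusted comparison of change scores. A change score uses the baseline inefficiently: at a correlation of 0.50 it is no more precise than the T1 score alone, although FES-I is measured on everyone at T0.

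The one explicit use of baseline data is to test for group differences. In groups formed by sound randomisation, such a test examines a null hypothesis already known to be true. Run before the main analysis, with no covariate set fixed in this document, it invites adjustment for whatever happens to be significant.

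At stake are precision and prespecification. The validity of the comparison is not in question. Precision has some practical weight, because 25–30% drop-out from 200 leaves 140–150, below the 154 the protocol says it needs.

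**Working it through.** **Inputs.** From {14}: f = 0.15, power 0.95, alpha 0.05, correlation ρ = 0.50, ε = 1, required N = 154, enrolment 200, drop-out 25–30%. From {8}: two arms, 1:1. Assumptions: two measurements (T0, T1) for a T1 outcome, with three also tried; equal FES-I variance at T0 and T1.

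**1. The plan's own figure.** For the within-between interaction with k groups and m measurements, the noncentrality is λ = f²·N·m/(1−ρ), with df (k−1)(m−1) and (N−k)(m−1). For k = 2 and m = 2, λ = 0.0225 × 2/0.5 × N = 0.09N. Power of 0.95 needs N = 147, or 148 in equal groups. With m = 3 the answer is 116. The stated 154 is not reproduced, but at N = 154 and m = 2 the power is 0.959, so it is slightly generous. This does not affect the ratios below.

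**2. What that test is.** With two time points, the interaction is the t-test on change. Its noncentrality is N·d²/4, so d²/4 = 0.09 and d = 0.6 SD of change. At ρ = 0.50 the SD of change equals the SD of FES-I.

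**3. Variance of the comparison, in units of the FES-I variance.**

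- change score: 2(1−ρ)
- T1 score alone: 1
- ANCOVA on baseline: 1−ρ²

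The gain is therefore 2/(1+ρ) over the change score and 1/(1−ρ²) over the T1 score. At ρ = 0.50 the variances are 1.00, 1.00 and 0.75. Both ratios are 1/0.75 = 1.33, and the standard error is multiplied by √0.75 = 0.866.

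| ρ | gain over change score | gain over T1 score |
|---|---|---|
| 0.3 | 1.54 | 1.10 |
| 0.4 | 1.43 | 1.19 |
| 0.5 | 1.33 | 1.33 |
| 0.6 | 1.25 | 1.56 |
| 0.7 | 1.18 | 1.96 |
| 0.8 | 1.11 | 2.78 |

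**4. In participants and power, at ρ = 0.50.** With ANCOVA, λ becomes 0.09N/0.75 = 0.12N. For 95% power, N falls from 148 to 112.

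| N analysed | power, change score | power, ANCOVA |
|---|---|---|
| 140 | 0.941 | 0.983 |
| 150 | 0.955 | 0.988 |
| 154 | 0.959 | 0.990 |

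With adjustment, 140 participants carry the information of 140 × 1.333 ≈ 187 without it.

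**5. The strata.** A simulation of 4,000 trials at N = 154 and ρ = 0.50 gave a gain of 1.33 for baseline FES-I alone. With three stratum terms unrelated to the outcome added, it was 1.31. The documents give no prognostic value for gender, couple status or statin intake, so no gain from the strata can be computed.

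**6. The entry cut.** Section {14} does not say whether 0.50 applies within the trial or in an unselected population. Suppose the latter, with normal scores and the FES-I ≥ 20 cut falling at the population mean (all assumptions). The baseline variance then shrinks to 1 − 2/π = 0.363. The change-score variance is 0.5² × 0.363 + 0.75 = 0.84, and the gain is 0.84/0.75 = 1.12 (simulated: 1.11).

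**The case against.** The strongest objection is that {20a} names no model at all. A reader might infer that the plan leaves baseline FES-I and the strata out of the analysis. The text does not say so: adjustment is neither specified nor excluded, this is a condensed article, and the preregistration and any analysis plan are not shown. Nor does the word reduction settle the matter. An ANCOVA of change with baseline as covariate gives the same group difference as an ANCOVA of T1, and a planning model does not bind the analysis model. This stands, and it limits the point to what the article indicates and leaves open.

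It does not remove the point. Both descriptions of the primary comparison and the sizing lean the same way, and the baseline tests in {18a} are a stated choice. At ρ = 0.50 the gain is the same whether the unadjusted comparison meant is of change or of T1 scores.

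A second objection is that {20c} removes non-adherent participants, so the analysed arms may differ at baseline by more than chance. That is correct, and it qualifies the argument that baseline tests can only detect chance. It does not make significance tests a good response, and baseline adjustment does not cure the selection either.

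Third, the unadjusted power for the planned effect is already 0.94–0.96 against a target of 0.95. That is true if f = 0.15 is right, and it makes this an improvement in efficiency rather than the repair of an invalid analysis.

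**Conclusion.** The point holds as a recommended improvement. The article describes the primary comparison without a model, its sizing corresponds to an unadjusted change score if two time points were used, and it plans baseline significance tests. Prespecified adjustment for baseline FES-I is worth about one third more participants at the protocol's own correlation of 0.50. That figure assumes 0.50 holds within the trial and that variances are equal at T0 and T1. Over a change score, the gain runs from 54% to 11% for correlations of 0.3 to 0.8, and it is about 11–12% under the entry-cut scenario above.

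Three stronger inferences are not supported:

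- **Omitting the strata makes the standard error too wide.** This is so only if they are prognostic, and the documents give no figure. All of the computed gain comes from baseline FES-I.
- **The FES-I ≥ 20 cut makes the comparison more sensitive to chance imbalance.** The cut applies to both arms before randomisation. With a linear relation, it leaves the slope of T1 on baseline unchanged and narrows the spread of baseline scores.
- **Adjustment is free.** The cost is small (1.33 falls to about 1.31 if the strata are non-prognostic), but it is not zero. A fixed couple stratum also does not model the correlation within couples.

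**What to change.** - **In {20a}:** state that the primary analysis is an ANCOVA of T1 FES-I on arm, baseline FES-I and the randomisation factors (female/male/couple, statin intake), reporting the adjusted mean difference with its 95% confidence interval. Allow for correlation within couples, for example with a cluster-robust standard error or a random couple effect. The strata are included because the randomisation used them.
- **Continuous secondary outcomes:** use the same form, each with its own baseline.
- **In {18a}:** replace the tests of pre-intervention group differences with descriptive baseline summaries by arm.
- **Consistency:** if the preregistration or an analysis plan already fixes a model, bring the article's wording into line with it.

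The cost is a paragraph of text and a few degrees of freedom. The covariates are already collected, and the planned software can fit the model. The protocol version is dated March 2024 and data collection runs to the second quarter of 2025, so on that timetable the model can be fixed before the outcome data are complete.
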